#### Breathing techniques group (BG)

Breathing technique (BT) is a self-management device in strict accordance with *WHO Europe, Support for Rehabilitation: Self-management After COVID-19-Related illness, Second Edition*. The leaflet was written by rehabilitation professionals in consultation with people recovering from COVID-19. For adults who are recovering from COVID-19, breathing technique can be used by individuals after hospitalization from the illness and those in the community who did not need hospitalization [29].

Breathing techniques exercises are performed as follows (Fig. 3).Controlled breathing helps in relaxing and controlling breathing. Patient is required to sit in the position with one hand on chest and the other on stomach. Relax and focus on breathing. Inhale slowly and smoothly through nose, exhale through mouth. The hand on stomach should rise more than the hand on chest.Paced breathing breaks the activity down into smaller parts. Inhale before making the effort of the activity. Exhale when making the effort of the activity. Note: this technique is carried out with activities that require more effort, such as climbing the stairs or walking up the hill.

**Fig. 3 Fig3:**
[figure not shown]
Breathing techniques group (BG). **a** Controlled breathing helps in relaxing and controlling breathing. Patient is required to sit in the position with one hand on chest and the other on stomach. Relax and focus on breathing. Inhale slowly and smoothly through nose, exhale through mouth. The hand on stomach should rise more than the hand on chest. **b** Paced breathing breaks the activity down into smaller parts. Inhale before making the effort of the activity. Exhale when making the effort of the activity. Note: this technique is carried out with activities that require more effort, such as climbing the stairs or walking up the hill

#### Kangyi Qiangshen Gong group (KQG)

KQG is the combination of Taiji, Yijinjing Qigong, Shaolin Neigong, Wuqinxi Qigong, Liuzijue Qigong, and Baduanjin Qigong. In conformity with the standard therapy, the KQG group will perform a standardized TCMR program of KQG which consists of seven sets of exercises in total [28].

Kangyi Qiangshen Gong exercises are performed as follows (Fig. 4).Preparation phasePosture 1: Starting form and warm-up. This posture consists of three poses including Ding Tian Li Di (Stand upright to touch the sky), Tong Zi Bai Fo (Child Worships Buddha), Yang Tou Wang Yue (Looking up to the moon).Pose 1: Stand upright to touch the sky (Ding Tian Li Di). Lift the hands slowly, press down. Raise hands in front of the chest, with knees slightly bent. Lift hands above the head, with palms facing up, fingertips facing, while standing on your toes. Stretch upward, hold for 5 s, return to standing position.Pose 2: Child worships Buddha (Tong Zi Bai Fo). Arms raised from the sides of body, parallel to the floor and stretch outwards, then hold for 5 s. Press palms together, flip hands 180°, and align the fingertips towards Dan Zhong acupoint, breathe naturally, hold for 5 s.Pose 3: Look up the moon (Yang Tou Wang Yue). Turn toes inward, support the back of neck with the right hand, and the back with the left hand. Raise the head to the right 45° and twist waist, hold for 5 s then return. Twist waist and look at the left heel, hold for 5 s. Support the back of neck with the left hand, and the back with the right hand. Raise the head to the right 45° and twist waist, hold for 5 s then return. Twist waist and look at the right heel, hold for 5 s.Practice phasePosture 2: Six sounds’ breathing exercise to exhale stagnated lung-qi (Liu Zi Hu Xi Xuan Fei Qi). This posture involves inhalation and exhalation through six different mouth patterns and sounds, which are the Xu, He, Hu, Si, Chui, and Xi. This is to regulate and control the rise and fall of the breath in the body.Pose 1: Xu. Put hands on waist with palms facing up. Stretch out the right arm 45° towards left front and say “Xu…”, return. Stretch out the left arm 45° towards right front and say “Xu…”, return.Pose 2: He. Bend the knees. Raise the arms forward with palms up. Press palms down and say “He…”, return.Pose 3: Hu. Put hands in front of abdomen, turn palms inwardly. Stretch forward with circle shape, and say “Hu…”, return.Pose 4: Si. Raise hands over chest. Push hands forward with palms upright and say “Si…”, then return.Pose5: Chui. Put hands in front of the abdomen. Wrap hands around to the sides of the body and press down, say “Chui…”, then return.Pose 6: Xi. Put hands in front of the abdomen, raise the palms above the head and open arms. Pull back and press down, say “Xi…”, then return.Posture 3: Expand and draw in chest to harmonize qi and blood (Kai He Kuo Xiong He Qi Xue). Cross arm over chest. Push palm towards, split apart and open arms and turn head to the left side. Hold for 5 s and return. Repeat on the other side.Posture 4: Push and pull hard to increase strength (Guan Jing Tui La Zeng Qi Li). Turn the toes inward. Put the hands on the waist with expanded chest and extended shoulders, hold for 5 s. Push hands forward with force until strength reaches the fingertips, then say “He…”, push forward and straighten the elbows. Hold for 5 s. After inhaling, pull the hands back quickly while saying “He…”, put the hands on waist.Posture 5: Fly obliquely to balance Yin and Yang (Tai Ji Xie Fei Tiao Yin Yang). Shift weight to the right, bend the knees, left empty step, hold hands in a circle, step to the left, pull the hands apart. Shift weight to the left, hold hands in a circle, step to the left, pull the hands apart.Posture 6: Lift the heels and stomp the feet to help eliminate diseases (Ti Zhong Dun Zu Xiao Bai Bing). Put hands around waist, slowly lift heels off the ground. Hold for 5 s and stamp on heels, return.Posture 7: Closing form (guide Qi to Dantian and regulate tendons and joints). Slightly bend the knees, cross hands over the chest. Open arms and kick left, return. Open arms and kick right, return. Cross hands over your chest, open arms outwards, return. Guide Qi to Dantian, return.

**Fig. 4 Fig4:**
[figure not shown]
Kangyi Qiangshen Gong group (KQG). (1) Preparation phase. Posture 1: Starting form and warm-up. This posture consists of three poses including Ding Tian Li Di (Stand upright to touch the sky), Tong Zi Bai Fo (Child Worships Buddha), Yang Tou Wang Yue (Looking up to the moon). **a** Pose 1: Stand upright to touch the sky (Ding Tian Li Di) Lift the hands slowly, press down. Raise hands in front of the chest, with knees slightly bent. Lift hands above the head, with palms facing up, fingertips facing, while standing on your toes. Stretch upward, hold for 5 s, return to standing position. **b** Pose 2: Child worships Buddha (Tong Zi Bai Fo). Arms raised from the sides of body, parallel to the floor, and stretch outwards, then hold for 5 s. Press palms together, flip hands 180°, and align the fingertips towards Dan Zhong acupoint, breathe naturally, hold for 5 s. **c** Pose 3: Look up the moon (Yang Tou Wang Yue). Turn toes inward, support the back of neck with the right hand, and the back with the left hand. Raise the head to the right 45° and twist waist, hold for 5 s then return. Twist waist and look at the left heel, hold for 5 s. Support the back of neck with the left hand, and the back with the right hand. Raise the head to the right 45° and twist waist, hold for 5 s then return. Twist waist and look at the right heel, hold for 5 s. (2) Practice phase. Posture 2: Six sounds’ breathing exercise to exhale stagnated lung-qi (Liu Zi Hu Xi Xuan Fei Qi). This posture involves inhalation and exhalation through six different mouth patterns and sounds, which are the Xu, He, Hu, Si, Chui, and Xi. This is to regulate and control the rise and fall of the breath in the body. **d** Pose 1: Xu. Put hands on waist with palms facing up. Stretch out the right arm 45° towards left front and say “Xu..”, return. Stretch out the left arm 45° towards right front and say “Xu..”, return. **e** Pose 2: He. Bend the knees. Raise the arms forward with palms up. Press palms down and say “He..”, return. **f** Pose 3: Hu. Put hands in front of abdomen, turn palms inwardly. Stretch forward with circle shape, and say “Hu..”, return. **g** Pose 4: Si. Raise hands over chest. Push hands forward with palms upright and say “Si..”, then return. **h** Pose 5: Chui. Put hands in front of the abdomen. Wrap hands around to the sides of the body and press down, say “Chui..”, then return. **i** Pose 6: Xi. Put hands in front of the abdomen, raise the palms above the head, and open arms. Pull back and press down, say “Xi..”, then return. **j** Posture 3: Expand and draw in chest to harmonize qi and blood (Kai He Kuo Xiong He Qi Xue). Cross arm over chest. Push palm towards, split apart, and open arms and turn head to the left hand side. Hold for 5 s and return. Repeat on the other side. **k** Posture 4: Push and pull hard to increase strength (Guan Jing Tui La Zeng Qi Li). Turn the toes inward. Put the hands on waist with expanded chest and extended shoulders, hold for 5 s. Push hands forward with force until strength reaches the fingertips, then say “He..”, push forward and straighten the elbows. Hold for 5 s. After inhaling, pull the hands back quickly while saying “He..”, put the hands on waist. **l** Posture 5: Fly obliquely to balance Yin and Yang (Tai Ji Xie Fei Tiao Yin Yang). Shift weight to the right, bend the knees, left empty step, hold hands in a circle, step to the left, pull the hands apart. Shift weight to the left, hold hands in a circle, step to the left, pull the hands apart. **m** Posture 6: Lift the heels and stomp the feet to help eliminate diseases (Ti Zhong Dun Zu Xiao Bai Bing). Put hands around waist, slowly lift heels off the ground. Hold for 5 s and stamp on heels, return. **n** Posture 7: Closing form (guide Qi to Dantian and regulate tendons and joints). Slightly bend the knees, cross hands over the chest. Open arms and kick left, return. Open arms and kick right, return. Cross hands over your chest, open arms outwards, return. Guide Qi to Dantian, return

### Adherence

This will be home respiratory training program with compliance assessed every week by telephone calls and review of the everyday charts filled-in by participants. The participants will be informed to perform breathing techniques or KQG exercises every day at 10 am and 4 pm. Remote monitoring devices will be offered to every ward so that remote monitoring of the training of the subject can be achieved. The participants will be required to sign in a recorded diary after each exercise.

### Outcome measurements

Researchers assessing primary outcomes were blinded for group assignment. The outcomes include Modified Medical Research Council Dyspnea Scale, Modified Borg Scale, Fatigue Scale-14, Patient Health Questionnaire-9 Scale, Pittsburgh Sleep Quality Index and Respiratory Symptoms Scale. Evaluation of the outcomes will occur at three points (pre-exercise, 3 months post-exercise, and 3 months follow-up).

### Primary outcome measurements

#### Modified Medical Research Council (mMRC) Dyspnea Scale

The mMRC Dyspnea Scale will be used as the primary outcome indicator to evaluate the dyspnea symptoms and physical health; mMRC score is a good indicator of the functional capacity of patients’ lungs [30]. The mMRC grades [31] are as follows: mMRC grade 0, dyspnea occurs only during strenuous exercise; mMRC grade 1—the patient has shortness of breath when walking on flat ground or walking on a small slope; mMRC grade 2—due to shortness of breath, when walking on flat ground, the patient is slower than another person of the same age or needs to stop to rest; mMRC grade 3—when walking on flat ground for approximately 100 m or after a few minutes, the patient needs to stop to pant; and mMRC grade 4—due to severe breathing difficulties, the patient cannot leave the house or has breathing difficulties when dressing or undressing. The mMRC score will be assessed with a repeated longitudinal analysis.

### Secondary outcome measurements

#### Modified Borg Scale

The Modified Borg Scale [32] will be used to assess the dyspnea symptoms and physical health. The participants will be required to walk for 6 min in a corridor with the distance of 30 m and to fill in the questionnaire or to describe verbally of the degree of dyspnea. The Modified Borg score grades are as follows: grade 0—no breathing difficulties; grade 1—very mild breathing difficulties or fatigue; grade 2—mild breathing difficulties or fatigue; grade 3—moderate breathing difficulties; grade 4—slightly serious breathing difficulties; grade 5—relatively serious breathing difficulties; grade 6—degree of breathing difficulties is between grades 5 and 7; grade 7—very severe breathing difficulties; grade 8—degree of breathing difficulties is between grades 7 and 9; grade 9—extremely difficult in breathing; grade 10—maximum degree of breathing difficulties (patient have extreme feeling of breathing difficulties, it is the most severe breathing difficulties that he/she has ever experienced). After all the patients finished the Borg Scale, the grade is classified into grade 0, grades 1 to 3, grades 4 to 6, and grade ≥ 7. All patients and their family dependent will sign the consent letter [33].

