**Methods/design:**

This is a parallel-design, two-arm, analyst assessor-blinded, randomized controlled trial. In total, 60 discharged patients with COVID-19 sequelae, aged from 20 to 80 years will be recruited and randomly assigned to the World Health Organization instructed breathing techniques (BT) group and the Kangyi Qiangshen Gong exercise prescription (KQG) group at a ratio of 1:1. The patients in the BT group will perform breathing techniques exercise, and the patients in the KQG group will perform KQG exercise. Both groups will perform exercises twice a day for 3 months. The primary outcome will be measured with the Modified Medical Research Council Dyspnea Scale, and the secondary outcomes will include the Modified Borg Scale, Fatigue Scale-14, Patient Health Questionnaire-9 Scale, Pittsburgh Sleep Quality Index, and the Respiratory Symptoms Scale. Clinical scales will be assessed at three points (pre-exercise, 3 months post-exercise, and 3 months follow-up). Adverse events will be recorded for safety assessment.

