**Fig. 1 Fig1:**
[figure not shown]
Flow chart of the trial. The present study is a randomized controlled trial. Sixty patients will be included and randomized equally to two groups, a BT group and a KQG group. For 30 patients in each group, this trial will include a 12-week treatment period. During the treatment, patients in the BT group will receive breathing techniques intervention, while the KQG group will receive KQG intervention. Both the outcome assessments will be performed at 3 time points, namely the baseline, the end of the treatments at 12 weeks, and 12 weeks of follow-up subsequently

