### Sample size calculation

The PASS software (PASS 11, NCSS, LLC, Kaysville, UT, USA) will be used to estimate the sample size utilizing two independent sample means (*α* = 0.05, *β* = 0.10). We will use the mMRC Scale as the primary efficacy outcome. Based on previous clinical studies on the effect of respiratory symptoms after KQG interventions, the mMRC Scale score in the control group is 0.74 with a standard deviation of 0.55, and the average mMRC Scale score in the treatment group is 1.52 with a standard deviation of 0.54 [25, 40, 41]. The target sample size will be 60 participants in each group based on 80% power, 5% type I error, and two-sided test, anticipating on maximum loss to follow-up of 20%.

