#### Analysis of primary outcome

The primary outcomes will be evaluated at baseline, 12 weeks after the intervention, and follow-up. We will conduct sensitivity analyses for missing data (intention-to-treat analysis) and for adjustment of covariates of physical activity (adjusted intention-to-treat analysis). The primary endpoint is the mean change in mMRC Scales from baseline to the follow-up day. Baseline covariates included are sex, age category, history of cardiopulmonary disease, and body weight category. The whole outcomes scale will be measured at baseline. When normally distributed, the data will be analyzed with unpaired *t*-test for comparison between two groups, while for multiple comparisons one-way ANOVA and repeated measures (RM) ANOVA will be used. A sensitivity analysis using multiple imputation techniques (imputation using chained equations) will be included to assess the effect of missing data on the primary outcome. Besides, we will compare participants randomly allocated to BT group or KQG group, who received an allocated treatment that was deemed to be of high fidelity. The percentage of missing data is 20% and 5 imputed datasets will be used for analysis, which is the minimum recommended number. Prior to any analysis, any missing data pattern will be investigated and the reasons for missing data will be obtained and patterns will be investigated to judge the plausibility of missingness assumptions.

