#### Analysis of secondary outcome

Analysis of secondary outcome will be undertaken referring to analysis of primary outcome. We will test for between arm differences for each endpoint specified. Chi-square test or Fisher’s exact test will be adopted to analyze the adverse events (AEs).

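### The protocol leaves open whether the Modified Borg outcome is the 0–10 grade or a four-class recode of it; analysing the classes would lose information

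*Protocol article*

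**What the plan says.** The abstract of the protocol article places Borg among the secondary outcomes: "the secondary outcomes will include the Modified Borg Scale, Fatigue Scale-14" and others. The Modified Borg Scale section defines grades 0 to 10, obtained around a 6-minute walk, and ends its description of the scoring by saying that, when every patient has completed the scale, "the grade is classified into grade 0, grades 1 to 3, grades 4 to 6" and, as the fourth class, 7 or above. That is the only handling of the data described for this scale in its own section.

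The analysis section adds one general rule: "Analysis of secondary outcome will be undertaken referring to analysis of primary outcome". The primary analysis is a mean change from baseline, and "When normally distributed, the data will be analyzed with unpaired *t*-test for comparison between two groups", with ANOVA and repeated-measures ANOVA for further comparisons. Chi-square and Fisher tests are named for adverse events only.

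On group size, the legend of Fig. 1 has "For 30 patients in each group, this trial will include a 12-week treatment period", whereas Sample size calculation has "The target sample size will be 60 participants in each group based on 80% power, 5% type I error, and two-sided test".

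**The concern.** The two instructions do not fit together. The Borg section recodes every grade once collection is complete. The analysis section prescribes comparisons of means. Either the class codes 0 to 3 are treated as numbers, although the classes span 1, 3, 3 and 4 grades, or the classes play no part in the analysis and the text does not say so.

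Two things are at stake. First, a choice between grade and class remains open and could be made after the data are seen. Second, if the class is chosen, real movement within a class disappears and a one-grade move across a boundary counts in full. Apart from the primary mMRC scale, Borg is the only outcome devoted to dyspnoea; the Respiratory Symptoms Scale lists dyspnoea as one of several symptoms. A blunter Borg analysis would therefore give weaker support to the primary result.

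**Working it through.** **1. What follows from the cut-points alone.** The classes are 0 | 1–3 | 4–6 | 7–10, coded 0, 1, 2, 3.
- 3 to 1: code 1 to 1, no change (a true fall of 2 grades).
- 6 to 4: code 2 to 2, no change (a true fall of 2 grades).
- 4 to 3: code 2 to 1, a full step (a true fall of 1 grade).

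This needs no assumption.

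**2. Is there a figure in the plan to reproduce?** No. The documents give no Borg mean, SD, effect or power. The only sample-size calculation concerns mMRC. The size of the loss must therefore rest on assumed inputs, shown as a range.

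**3. Assumed inputs.** A normal score rounded to whole grades and held within 0–10; the same SD in both arms before rounding; arm means 1 point apart, the lower mean running from 1.5 to 4 in steps of 0.5; SD 1.3, 1.5, 2 and 2.5. Exact grade probabilities were used, with no simulation.

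**4. Formulas.** Standardised difference d = (difference in arm means) / √(average of the two arm variances), computed once on the grade and once on the class code. Relative efficiency = (d_class / d_grade)². Loss = 1 − relative efficiency. Power is for a two-sided t-test at 5% (noncentral t).

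**5. One case in full** (means 3 and 4, SD 1.5).
- Grade: 0.990 / 1.512 = 0.655.
- Class: 0.337 / 0.580 = 0.581.
- Relative efficiency: (0.581 / 0.655)² = 0.79, a loss of 21%.
- Power at 30 per arm: 70% on the grade, 60% on the class. At 60 per arm: 95% and 88%.

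**6. Range over the arm means.**

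| Assumed SD | Loss | Power at 30 per arm, grade → class | Power at 60 per arm, grade → class |
|---|---|---|---|
| 1.3 | 24.3–29.8% | 81.2–81.7% → 66.5–70.2% | 98.2–98.3% → 92.5–94.4% |
| 1.5 | 21.4–22.8% | 69.3–70.4% → 58.8–60.0% | 94.0–94.5% → 87.6–88.4% |
| 2 | 10.8–14.9% | 44.9–47.0% → 40.9–41.5% | 74.3–76.7% → 69.4–70.2% |
| 2.5 | 5.7–11.5% | 30.4–32.5% → 29.0–29.7% | 54.2–57.5% → 51.8–53.0% |

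Both group sizes are shown because the article gives both. The percentage loss does not depend on which is right; the power does.

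**7. Wider check.** For a small shift, with means from 1 to 5 and SD from 1 to 2.5, the loss runs from 3% to 46% (median about 16%). If all 11 grades are equally frequent it is about 9%. The classes lost information in every case tried, and the loss depends strongly on the spread of the grades.

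**The case against.** The strongest reply is that the protocol never makes the class the endpoint. It says that grades are classified, not that classes are compared, and the general rule points to tests of means, which suit the numeric grade. PHQ-9 also has severity bands, and its section still announces a longitudinal repeated-measures analysis, so bands and an outcome analysis can sit side by side in this article. The lack of such a sentence for Borg proves little, since Fatigue Scale-14 and PSQI lack it too. One may add that the choice between score and band is a detail that an article can leave to the analysis plan.

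Most of this stands. A reader might infer that the score is certainly collapsed before analysis; the text supports this only as one of two readings. The last argument does not dispose of the point, however. The article is not silent: it states a recode for every patient that fits poorly with its own analysis section.

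A reader might also infer a fixed loss, such as a quarter. The documents cannot support a single figure, because they say nothing about the Borg distribution; losses of that size need a narrow spread. Nor do they support calculating power for a chi-square test on the classes, since they assign that test to adverse events only.

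**Conclusion.** The point holds as an unresolved conflict between the Modified Borg Scale section and the analysis section, leaving two candidate endpoints. If the classes are analysed, within-class change is invisible and information is lost: about 21–30% at SD 1.3–1.5 and about 6–15% at SD 2–2.5, assuming a 1-point difference and roughly normal grades. If the 0–10 grade is analysed, nothing is lost and only the wording needs repair.

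Borg is secondary, and both the sample size and the primary endpoint rest on mMRC, so the primary conclusion is not affected. Any statement about Borg power also depends on the unreconciled group size, 30 in the Fig. 1 legend against 60 in Sample size calculation.

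**What to change.** Add one sentence to Analysis of secondary outcome: the Modified Borg outcome is the 0–10 grade, compared between arms at 12 weeks and at follow-up with the baseline grade as covariate; the four classes serve descriptive tables only. Make the Borg section agree.

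The baseline covariate is worth stating. With equal variances and a baseline-to-outcome correlation ρ, the variance under adjustment relative to a change score is (1 − ρ²) / [2(1 − ρ)] = (1 + ρ) / 2, which never exceeds 1.

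This is a free improvement. The grade is already scheduled at all three time points, so no visit, form or patient is added, and the descriptive classes are kept. It also removes a choice that could otherwise be made after seeing the data. The two statements of group size should be reconciled separately.
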